### 2.2 Conditions

#### 2.2.1 Participants

In every study country, 15 OPDs and 15 DCPs will be recruited and participate to the experimentation, for a total of 45 OPDs and 45 DCPs (90 people overall). OPDs and DCPs’ inclusion and exclusion criteria are summarized below (Table 1).

**TABLE 1 T1:** Participants’ selection criteria.

Type of participants	Inclusion criteria	Exclusion criteria
OPDs	• Interest in the project and signed consent form • Age 65 + • To be able to see, hear and move • Diagnosis of MCI or dementia with mild to moderate impairment (MoCA total score ≥ 10/30) • Absence of aphasia (mild acceptable) • Be able to understand and undertake simple task as required during activities	•Lack of consent to participate • Age 65− • Not be able to see, hear and move even with the help of appropriate aids • Absence of formal diagnosis of MCI or dementia or severe level of impairment (MoCA total score ≤ 10/30) • Moderate to severe aphasia • Not able to understand and undertake simple task as required during activities
DCPs	• Having experience in the dementia field (e.g., educators, occupational therapists, physiotherapists, psychologist, sociologists, nurses, music therapists, professional caregivers, doctors) • Having interest in the project and signed consent form • For the (co-)facilitators and internal/external observers: having completed the SOUND training	• Lack of experience working in the dementia field • Lack of consent to participate • For the (co-)facilitators and internal/external observers: lack of completion of the SOUND training

Older people with dementias will be recruited from the study organizations, health care dementia services and community services such as diagnostic centers, dementia day care centers, residential care facilities and charities. Individuals will already have a formal diagnosis of MCI or dementia. Their level of cognitive impairment is routinely assessed by the health professionals of the organization to which they belong. Therefore, these health professionals will support the recruitment and selection processes. Ethical approval has been obtained depending on the national legal requirements. OPDs retention will be empowered by collaborating with their professional caregivers who will present the SOUND activities as a pleasant novelty and as a gift.

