The Frontal Assessment Battery (FAB) is a short neuropsychological tool aiming to assess executive functions or functions related to the frontal lobes and correlated with frontal metabolism (Sarazin et al., 1998). It includes 6 subtests one for each investigated cognitive function: similarities test (conceptualization and abstract reasoning); verbal fluency test (mental flexibility); Luria motor sequences (motor programming and executive control of action); conflicting instructions (sensitivity to interference); go–no go test (inhibitory control); prehension behavior (environmental autonomy). The scoring for each subtest is from 0 to 3, for a maximum total score of 18 (highest performance). The battery has good validity (correlation of ρ = 0.82 with the Mattis Dementia Rating Scale) and interrater reliability (κ = 0.87) (Dubois et al., 2000).

The Hospital Anxiety and Depression Scale (HADS) is a 14-item self-report measure for screening anxiety (7 questions) and depression (7 questions) states. The Likert-scale ranges from 0–3 for a maximum total score of 21, with higher scores indicating greater anxiety and depression, and with a cut-off > 10 (Zigmond and Snaith, 1983). It has shown high concurrent validity with other widespread anxiety and depression assessments and has proved a 20-day test-retest reliability of0.94 (Michopoulos et al., 2008). It is widely used in the field of dementia as it is brief, measures both anxiety and depression and is suitable for people with physical comorbidities (e.g., Clare et al., 2012).

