## 3 Discussion

To the best of our knowledge, SOUND is one of the few studies focusing on the impact of a music-based intervention on both dementia care professionals and older people with dementia, since the available studies are targeted to older people mainly (e.g., Hyde et al., 2009; Daykin et al., 2017; Habibi et al., 2017; Brancatisano et al., 2019; Domínguez-Chávez et al., 2019). Conversely, in this study, the former and the latter, are conceived by the protocol as distinct but also intertwined targets. They build together a unique care ecosystem that can be well-represented and interpreted by the circle, that is a democratic setting able to overcome the care asymmetry between care professionals and patients.

The intervention is innovative, because it is delivered in circle, it is led by facilitators with the support of other care professionals, all trained on the method through an original curriculum, and it includes different types of music activities both passive and active, highly personalized as based on the beneficiaries’ preferences and attitudes collected before the intervention finalization.

The protocol has been designed based on the recommendations of Moreno-Morales et al. (2020) by including well-focused outcome measures and discussing how the findings may improve the well-being of OPDs and DCPs.

Since the effects of music are not immediate (Moreno-Morales et al., 2020), SOUND was conceived as a progressive and continuous intervention to obtain successful results (Leubner and Hinterberger, 2017) and it foresaw both pre-post evaluation and medium-term follow-up.

In light of the above, with regard to OPDs we expect: (a) an increase of ± 10 points with 95% confidence interval in the WHO-5 percentage scores regarding wellbeing; (b) no decrease in MoCa and FAB scores regarding cognition; (c) a 50% reduction of the HADS score or absence of depression and anxiety concerning mood; (d) a decrease of 2 points corresponding to the median value for the BPSD symptoms and caregivers distress in the NPI; (e) a negative variation, e.g., of 0.5–1 points toward 0, in the LEWT as an index of improved emotional wellbeing.

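### The 14-item HADS is given a maximum total of 21, its cut-off is tied to no score, and the mood and cognition expectations can be met without change

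*Protocol article*

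**What the plan says.** Section 2.3.2 of the protocol article introduces the HADS as a "14-item self-report measure for screening anxiety (7 questions) and depression (7 questions) states". For the scoring it then states: "The Likert-scale ranges from 0–3 for a maximum total score of 21". The same sentence goes on to say that a high score is unfavourable and sets a threshold of more than 10. It does not say whether the 21 or the cut-off belongs to a subscale or to the sum of all items.

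The Discussion (section 3) lists what the authors expect for OPDs. For mood it is "a 50% reduction of the HADS score or absence of depression and anxiety concerning mood"; for cognition it is "no decrease in MoCa and FAB scores regarding cognition". Neither comes with a margin or a baseline condition.

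Three other places bear on how these can be read. The OPD entry criteria in Table 1 (section 2.2.1) set a cognitive threshold, "Diagnosis of MCI or dementia with mild to moderate impairment (MoCA total score ≥ 10/30", but no minimum HADS score. The sample is "for a total of 45 OPDs and 45 DCPs (90 people overall"; section 2.2.2 has the OPDs receive the intervention and describes no comparator. Section 2.4 names a paired t-test for comparisons between time points, with significance at p < 0.05.

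**The concern.** The stated HADS maximum contradicts the item count and item range in the same paragraph. That matters beyond the slip, because the Discussion's absence of depression and anxiety needs a cut-off, and the cut-off needs a score to be applied to. With three countries scoring the instrument, one site could classify people on the sum and another on the subscales.

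The mood expectation has a second weakness. It joins a relative reduction to a state by an *or*. The state can already hold at T0, since no minimum symptom level is required for entry. People without symptoms would then count towards the expected result although nothing changed in them.

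The cognition expectation is that something does not happen. Without a margin, and with a test of difference as the only named temporal comparison, the plan gives no way to support it. At stake is what the pilot can say about mood and cognition, and what it hands on to the larger study that it is meant to prepare.

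**Working it through.** **1. The HADS maximum.** Inputs from section 2.3.2: 14 items, 7 per subscale, each scored 0–3. Maximum = number of items × highest item score.

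- All items: 14 × 3 = 42. The stated total of 21 is not reproduced.
- One subscale: 7 × 3 = 21. The stated figure is reproduced here.

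The same rule reproduces the other maxima checked in that section: FAB 6 × 3 = 18, WHO-5 5 × 5 = 25, NPI 12 × 4 × 3 = 144, NPI distress 12 × 5 = 60. The HADS figure is the exception.

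**2. The cut-off.** The lowest score above 10 is 11. On a subscale this is 11/21 = 52% of the range; on the total it is 11/42 = 26%. Take a person with 6 on anxiety and 6 on depression:

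- Subscale reading: 6 and 6 are both at or below 10, so a non-case on both.
- Total reading: 6 + 6 = 12, above 10, so a case.

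**3. The mood expectation under zero change.** Suppose each person's T1 score equals the T0 score. Nobody with a non-zero score meets the 50% arm. Everyone at or below the cut-off at T0 meets the absence arm. The number is 45 × p, where p is the share below the cut-off at T0. The article gives no p, so a range is assumed:

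| Assumed p | 45 × p |
|---|---|
| 0.5 | 22.5 |
| 0.7 | 31.5 |
| 0.9 | 40.5 |

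That is about 22 to 40 of 45 OPDs meeting the expectation with no effect.

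**4. The cognition expectation read through the paired t-test.** Inputs: n = 45 (section 2.2.1); α = 0.05 (section 2.4), taken as two-sided because sidedness is not stated. Assumed: a true mean MoCA decline of 1 point and an SD of individual change of 2, 3 or 4.

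Non-centrality = −(1/SD) × √45, with √45 = 6.708. The critical value is t(0.975; 44 df) = 2.015. The miss probability is the chance that the t statistic does not fall below −2.015 under the non-central t distribution.

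| SD of change (assumed) | Non-centrality | Probability of no significant decrease |
|---|---|---|
| 2 | −3.354 | 0.093 |
| 3 | −2.236 | 0.410 |
| 4 | −1.677 | 0.625 |

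With no true change at all, the probability of no significant decrease on one test is 0.975. So a reading based on non-significance becomes easier to satisfy as the data get noisier. A smaller sample acts the same way: at n = 36 (20% loss, assumed) and SD 3 the miss probability is 0.506.

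**The case against.** Several points on the other side stand.

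- A reader might infer that the article applies the cut-off to the total, and so uses a wrong scoring rule. It does not say that. The 7 + 7 split comes just before the 21, and 21 and the cut-off both fit a subscale, so a mislabelled subscale maximum is the likeliest explanation. What the text shows is ambiguity.
- A reader might also infer that the HADS slip tilts the study towards a positive report. It would not. Applying the cut-off to the total labels more people as cases, so fewer would meet the absence arm; the 6-and-6 person would fail it.
- The mood and cognition statements are expectations in a Discussion, for secondary outcomes of a pilot. They are not decision criteria. Nor does the article say that the mood item will be reported as a rate of individual responders; the count in step 3 assumes so.
- It is tempting to say that the plan will read a non-significant t-test as no decline. The article never states this. The test is in one section and the expectation in another, and the link is an inference. A margin may also be set in a fuller plan that is not shown.
- The 50% arm does require change. In a disease that is often progressive, stability is a reasonable hope. But with no comparator described and about 9 weeks from T0 to T2 (1 + 6 + 2), stability cannot be told apart from no effect.

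None of this removes the wrong maximum, the unassigned cut-off, or the fact that the absence arm can be met at baseline.

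**Conclusion.** The point holds in a limited form. By the article's own figures the HADS total runs 0–42, and 21 is the maximum of one subscale. This is certain and needs no outside source. The cut-off above 10 has no defined score, and the two readings classify some people differently.

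The mood expectation can be met without change through its absence arm. How often depends on the unknown baseline share: about 22 to 40 of 45 for an assumed 50–90%, and only if it is reported per person. The cognition expectation has no margin. The miss rates of about 9%, 41% and 63% rest on an assumed 1-point decline and SDs of 2, 3 and 4, and apply only if non-significance were taken as evidence of no decline.

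The primary OPD outcome, the WHO-5, is unaffected, and no sample size depends on any of this. Severity is minor to moderate: it should be corrected before scoring and analysis, but it does not undermine the study.

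**What to change.** 1. In section 2.3.2, state anxiety and depression as 0–21 each and the total as 0–42. Say that the cut-off applies to each subscale, and which score the 50% reduction refers to.
2. Report mean change on each subscale with its 95% confidence interval. Compute the rate of 50% reduction or absence only among OPDs above the cut-off at T0, and give that denominator.
3. For MoCA and FAB, report mean change with its 95% confidence interval. Do not claim absence of decline from a non-significant test. Make that claim only if a margin was stated in advance and the lower limit of mean change lies above minus that margin.

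The cost is a change of text and scoring syntax, with no new data or participants. The responder rate will have a smaller denominator and a wider interval, and a claim of preserved cognition becomes harder to make.

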#### 2.3.2 Pre-post and longitudinal tools

Concerning DCPs, an *ad hoc* questionnaire has been developed to investigate the level of stress and cooperation of professionals before and after the intervention. Beyond the demographic questions (i.e., age, gender, nationality, marital status, education), the pre-intervention questionnaire includes *ad hoc* questions on: (a) work condition (e.g., position, role, activities); (b) music attitudes; (c) well-being, motivation, satisfaction and self-realization at work (d) teamwork, (e) relationship with patients and family caregivers. Additionally, the Burnout Assessment Tool (BAT) will be administered for evaluating the work-related stress. Respondents can answer all the questions (i.e., both *ad hoc* questions and the BAT battery) through a five-point Likert scale, where 1 represents the lower and 5 the higher score/frequency. The post-intervention questionnaire for DCPs follows the same structure of the pre-intervention ones, except for quantitative and qualitative questions asking to what extent and how the intervention has improved every area e.g., well-being, team work, relationship with OPDs.

The Burnout Assessment Tool (BAT) is a self-assessment questionnaire that measures parameters associated with burnout (De Beer et al., 2020; Schaufeli et al., 2020) validated in Italy (Angelini et al., 2021; Borrelli et al., 2022), in Romania (Oprea et al., 2021), in Portugal (Sinval et al., 2022) and with European cut-off scores (Schaufeli et al., 2023). The BAT contains four different subscales: exhaustion, mental distance, loss of emotional control and loss of cognitive control. In addition, there are two sub-dimensions: psychological disorders and psychosomatic disorders. In total, the questionnaire consists of 33 items (23 for the reduced version), each with a 5-point scale (1 = never, 2 = rarely, 3 = sometimes, 4 = often and 5 = always). The total score is obtained by summing the points. A difference of ± 10 points with a 95% confidence interval shows significance in the variation of burnout (Daniels et al., 2022). The BAT will be the tool to assess the primary outcome for DCPs.

For the OPDs, demographic and baseline data will include age, gender, nationality, marital status, education, living condition, dementia service they attend, type of diagnosis, time of diagnosis, level of verbal expression and comprehension. As outcome tools, the following psychometric and standardized measures will be used.

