The WHO Wellbeing Index (WHO-5) is a self-assessment tool to measure the subjective mental well-being of individuals which is validated for older people (Heun et al., 1999). It includes five items each scored from 0 to 5. The total score ranges from 0 to 25, with higher scores indicating greater mental well-being. Scores < 13 indicate poor well-being and suggest depression according to the criteria of the International Statistical Classification (Tiganov et al., 1997). It is recommended to transform the raw scores to percentage scores, by multiplying it by 4, for data analysis when investigating change over time (Topp et al., 2015). Low mood may be suggested by a percentage score of ≤ 50 whilst a score of ≤ 28 may indicates depression. Similar to Kikuchi et al. (2023), a variation of ± 10 points of the percentage score with 95% confidence intervals will be considered significant. The reliability and validity of the WHO-5 is well established (e.g., Bech, 2012; Takai et al., 2013). The WHO-5 will be the tool to assess the primary outcome for OPDs.

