#### 2.4 Data analysis

The analysis plan includes, for quantitative data, outcomes description. Normality in distribution of continuous variables will be assessed via Shapiro-Wilk test and the following measures will be reported: mean and standard deviation for normally distributed variables or median and interquartile range for non-normally distributed variables. Absolute frequency and percentage will be reported for categorical variables. Comparisons between outcomes and exposures will be made using the Chi Square test, (in the case of categorical variables) or *t*-test or F-Anova (in the case of comparisons between normally distributed continuous variables and the groups), or by non-parametric tests such as Wilcoxon rank-sum test or Kruskal-Wallis test (in the case of comparisons between non-normally distributed continuous variables and the groups). Through Pearson’s or Spearman’s correlation we are going to study the relationship between continuous variables as appropriate according to variables’ distribution. Temporal comparisons (T0 vs. T1, T0 vs. T2, or T1 vs. T2) will be conducted by *T*-test for paired samples. Possible multivariate models will be assumed in case of significant differences in outcomes at the univariate level: coefficients and standard errors or odds ratios and 95% confidence intervals will be reported according to the typology of outcomes (continuous or binary). Goodness of fit will be determined by R-squared of pseudo R-squared as appropriate. Subjects withdrawing from the study will not be replaced, according to the intention to treat (ITT) principle. Sequential imputation using chained equations method will be applied in case of missing values in covariates. Statistical analyses will be conducted by a statistician, who will be blind to group allocation prior to analysis. The significance threshold will always be set at p < 0.05. The software used for the analyses will be SPSS for Win V24.0 (SPSS Inc., Chicago, IL, USA).

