Concerning the impact of the intervention on DCPs, we expect that: (a) the BAT scores will decrease by ± 10 points with a 95% confidence interval; (b) well-being at work, teamwork cooperation and communication with the OPDs will improve of one point on the five-point Likert scale for at least half of the items in each area. For example, to the question “How do you rate the quality of your relationship with older people with dementia?” we expect a minimal change from “Fair” to “Quite good”; (c) the LEWT scores will show a trend toward 0.

It is methodologically worth mentioning that this protocol was designed for DCPs daily working in a dementia care facility. However, the methodology may be applied even by external professionals who have an external collaboration with service providers. In this case, the impact of the caregiver stress, that may be influenced by working in a new workplace, could be measured by adding a question such as “In what way the delivery of the SOUND method in an unusual workplace have influenced your levels of work-related stress?”

One strength of the protocol lies in the use of both quantitative and qualitative data collection tools, and in a multi-method approach that will allow to gather written and visual data that will generate numerical, textual and narrative results. Another strength is the cross-national nature of the study that can provide interesting culture-based tips, since every team will use popular and traditional songs belonging to their context.

One limitation of the study may concern the small sample size at national level that will not allow a generalization of the results. Moreover, the protocol does not foresee the monitoring of clinical parameters such as cortisol, blood pressure as recommended by Uğur et al. (2016). In fact, although it would have been interesting to check the impact of the intervention on these realms, the study did not receive enough funding to cover the expenses for a biochemical investigation.

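### Both primary outcomes carry two incompatible meanings of significant: a ±10-point change with a 95% confidence interval, and p < 0.05 always

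*Protocol article*

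**What the plan says.** For people with dementia, section 2.3.2 of the protocol article states "The WHO-5 will be the tool to assess the primary outcome for OPDs" and gives the rule that "a variation of ± 10 points of the percentage score with 95% confidence intervals will be considered significant". For professionals, the same section makes the BAT the primary tool and states "A difference of ± 10 points with a 95% confidence interval shows significance in the variation of burnout". The BAT total is a sum of item scores, and the section says "the questionnaire consists of 33 items (23 for the reduced version" in parenthesis) without stating which version the 10 points belong to.

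Section 2.4 sets one criterion for every analysis: "The significance threshold will always be set at p < 0.05". On contrasts it says "Temporal comparisons (T0 vs. T1, T0 vs. T2, or T1 vs. T2) will be conducted by" a paired t-test, and it ranks none of the three above the others.

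The Discussion (section 3) turns the thresholds into expectations: "an increase of ± 10 points with 95% confidence interval in the WHO-5 percentage scores regarding wellbeing" and "the BAT scores will decrease by ± 10 points with a 95% confidence interval".

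**The concern.** Section 2.3.2 attaches the word significant to a change of fixed size. Section 2.4 attaches it, without exception, to a p-value. A result can meet one and fail the other, and the article gives no order of precedence. The 10-point rule itself has at least two readings for a group result: the mean change reaches 10, or the whole 95% confidence interval lies beyond 10. An increase of ±10 and a decrease of ±10 are also contradictory as written, because each verb gives one direction and the symbol gives two.

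These sentences govern the two headline results, well-being in people with dementia and burnout in professionals. If they stay as they are, the criterion can be picked once the data are known.

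**Working it through.** **Inputs.** n = 45 in each population (section 2.2.1). Threshold 10 points (section 2.3.2). Paired t-test and p < 0.05 (section 2.4); two-sided is assumed, to match a 95% interval. The article gives no SD of change and no power calculation, so there is no stated figure to reproduce. The SD is an assumption, shown from 10 to 40 points.

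**Formulas.** The 95% half-width is h = t(0.975, 44) × SD / √45, with t ≈ 2.015. The smallest mean change that passes is:
- p < 0.05 (interval excludes 0): h
- mean change reaches 10: 10
- 95% interval wholly beyond 10: 10 + h

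For SD 15: h = 2.015 × 15 / 6.708 = 4.51.

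| Assumed SD | p < 0.05 | Mean at least 10 | Interval beyond 10 |
|---|---|---|---|
| 10 | 3.0 | 10 | 13.0 |
| 15 | 4.5 | 10 | 14.5 |
| 20 | 6.0 | 10 | 16.0 |
| 25 | 7.5 | 10 | 17.5 |
| 30 | 9.0 | 10 | 19.0 |
| 40 | 12.0 | 10 | 22.0 |

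The arithmetic uses only n, the SD and the 10 points. It therefore serves the BAT as well as the WHO-5, each with its own SD.

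**Opposite verdicts from the same data (n = 45).**
- Mean +6, SD 15: interval 1.5 to 10.5, p = 0.010. Significant under section 2.4, short of 10 points.
- Mean +12, SD 15: interval 7.5 to 16.5, p < 0.001. Passes the test and the point-estimate reading, fails the confidence-limit reading.
- Mean +11, SD 40: interval −1.0 to 23.0, p = 0.07. Reaches 10 points, not significant under section 2.4.

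**If the true mean change is exactly 10**, the chance of passing at SD 15, 20 and 25 is 99%, 91% and 75% under p < 0.05, 50% under the point-estimate reading, and 2.5% under the confidence-limit reading.

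**BAT scale.** Items score 1 to 5. With 33 items the sum runs from 33 to 165, a width of 132, and 10/132 = 7.6%. With 23 items it runs from 23 to 115, a width of 92, and 10/92 = 10.9%.

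**The case against.** The best defence is that the 10 points are a relevance threshold, taken from cited sources and meant to stand beside the test. A 95% interval that excludes 0 is the same as two-sided p < 0.05, so 10 points with a 95% interval could mean both together. That is a sensible intention, and the fix below builds on it. But the text calls the 10-point change significant and never separates the two ideas.

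A reader might infer from the ± that a 10-point worsening would count as success. The documents do not support that. The Discussion names an increase for the WHO-5 and a decrease for the BAT, and section 2.3.2 says that higher WHO-5 scores mean better well-being. The ± there may only mean that change either way is notable. What stands is a contradictory sign.

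A reader might also infer that three unadjusted contrasts push false positives far above 5%: about 12% per outcome by simulation, and about 23% over both. That should not be claimed. The 12% counts significant worsening and the T1 to T2 contrast, and it ignores the 10-point rule. With no true change, a favourable result on T0 to T1 or T0 to T2 occurs in about 4.5% of trials. The 23% pools two populations with separate questions.

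It is also fair that an article may leave the primary contrast and the BAT version to the full plan. They are raised here only because the conflicting rule cannot be repaired without them. Finally, this is a pilot of feasibility and preliminary effects, which lowers the stakes. It does not make the two rules agree.

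**Conclusion.** The point holds as a conflict in the stated decision rule for both primary outcomes. At assumed SDs of 15 to 25, the smallest mean change that counts ranges from 4.5–7.5 points to 14.5–17.5 points according to the reading. The exact gaps rest on the assumed SD, 45 complete pairs and a two-sided test. The disagreement itself appears at every SD tried from 10 to 40; at SD 40 the order of the first two rules reverses.

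The point does not extend to an inflated error rate or to worsening being declared a success. It is a should-fix: no confirmatory decision is tied to the threshold, but the article plans papers on these two effects, and their criterion should be fixed before analysis.

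**What to change.** - In section 2.3.2, delete the wording that makes a 10-point change significant, for both the BAT and the WHO-5.
- Define statistical significance only by the paired comparison: the 95% interval for the mean change excludes 0, the same as two-sided p < 0.05.
- Report separately whether the mean change reaches a signed relevance threshold: +10 WHO-5 percentage points, −10 BAT points.
- Remove the ± from both expectations in the Discussion.
- Name T0 to T1 as the primary contrast, with T0 to T2 and T1 to T2 as secondary.
- State which BAT version is used and which version the 10 points refer to.

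The cost is about one paragraph. No new data are needed, and the test in section 2.4 is unchanged. Keeping the test and the threshold apart matters. Merged into one success rule (mean of at least 10 and an interval excluding 0), the chance of success at a true change of 10 would fall from 99%, 91% and 75% to about 50% at SDs of 15, 20 and 25.
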